### Ethics

The Research Ethics Committee Arnhem-Nijmegen has waived formal ethical approval for this study, indicating it is not included in the Medical Research Involving Human Subjects Act. Eligible patients will be informed about the study by a member of the treatment team in the standard care pathway. While regular care continues as planned, patients are given sufficient time to consider participation in the study. Informed consent will be obtained before the collection of data by the coordinating researchers. Patients will be followed-up until the end of this study or until they withdraw consent. Due to the observational character of this study, participation poses no burden or risk for the participants. Participation leads to evaluation and may lead to improvement of the hepatitis care in addiction care facilities in the future, which benefits patients. Patients who decline participation in this study will still be offered access to onsite HCV care if the addiction care team can provide it.

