**Aims:**

With this study we aim to (1) eliminate 90% of identified HCV infections in Dutch addiction care, using a decentralized PWUD-HCV care model, and (2) identify facilitators and barriers for successful implementation of the model using interviews.

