### Study population

In Part 1 addiction care physicians will invite consecutive people who inject(ed) drugs or have other risk factors for HCV infection and who visit the CAC addiction care centers to participate. In order to be eligible for this study, a subject must be aged 18 years or older and able and willing to give informed consent. For the duration of the project, as many patients as possible will be included. There are no exclusion criteria for this study. Patients will be followed-up until the end of their HCV care journey. Since the CAC pathway is standard care in a decentralized setting, no comparison group can be formed. In part 2 we will invite addiction care physicians, nurses and addiction care policy makers employed both in centers participating in CAC and centers who do not.

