### Study outcomes

The primary outcome in part 1 is HCV viral elimination, defined as percentage of patients that achieved SVR among identified HCV RNA positive patients. Secondary outcomes are total number of patients tested, prevalence of HCV antibody and RNA positivity among tested patients, fibrosis stage in HCV positive patients as found by FIB-4 and/or Child–Pugh scores, decentralized treatment initiation rate, treatment completion, sustained virologic response rate and referral. The main study outcomes for part 2 are the barriers and facilitators contributing to (un)successful implementation of the HCV care pathway for PWUD in the Netherlands.

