### Data collection and management

The main study parameters collected are: acceptance rate of (on-site) testing, HCV prevalence, treatment acceptance rate, sustained virologic response (SVR) rates and re-infection rates. Furthermore, we will collect data on patient characteristics such as sex, age, history of drug use, medical history and comorbidities (including previous HCV infection and treatment), concomitant medication and available HCV-related clinical data (e.g. other risk factors, blood test results, liver fibrosis stage). All these parameters are stored in the electronic patient files by the patient’s treatment team as part of standard care. Data will then be collected anonymously by a member of the research staff according to the medical code of conduct [23]. A validated and GCP compliant data management program, CastorEDC, will be used for central data storage.

Interview recordings in part 2 of the study will be anonymized and used solely by the researches. The interview guide will address the following topics: preferred role of addiction center in HCV care: specifically for diagnosis, treatment and follow-up; experience and viewpoint on fully decentralized HCV care; real and anticipated barriers and facilitators for successful and sustainable implementation. Interviewee data collected includes participant characteristics such as sex, age, occupation and years of experience.

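### The primary percentage is defined over all identified RNA-positive patients, but only consenting patients supply data and consent is not tied to testing, so it can be biased, most likely upward

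*Protocol article*

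**What the plan says.** Four statements in the protocol article bear on this point.

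- **Target.** The first aim is to "eliminate 90% of identified HCV infections in Dutch addiction care". Study outcomes defines the primary outcome as the "percentage of patients that achieved SVR among identified HCV RNA positive patients". The denominator is everyone found to be RNA-positive.
- **Who enters.** Study population has physicians invite consecutive at-risk visitors, but a subject must be "able and willing to give informed consent".
- **When consent is given.** Ethics says: "Informed consent will be obtained before the collection of data by the coordinating researchers". It also says: "While regular care continues as planned, patients are given sufficient time to consider participation in the study". Data collection and management explains that the care team records the parameters in routine files and that research staff extract them afterwards.
- **Who stays outside.** Ethics says: "Patients who decline participation in this study will still be offered access to onsite HCV care", on condition that the local team is able to provide it.

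The parameters to be collected include "acceptance rate of (on-site) testing, HCV prevalence, treatment acceptance rate". The article describes no count, even in aggregate, of RNA-positive patients who did not consent. The limitations in the Discussion cover people who do not seek care, but not selection by consent.

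**The concern.** The denominator as defined and the denominator the data can supply are different groups. The first is all identified RNA-positive patients; the second is those who also consented. Nothing requires consent before the RNA result. A patient who tests positive and drops out of contact before consenting leaves no study record and has probably not reached SVR, so the percentage rises when that patient is left out.

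The Background places the main losses at this stage. In the earlier studies it cites, a median of 50% saw a specialist after a positive test and 53% of those started treatment, whereas loss during and after treatment was 2.5% and 7.1%.

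The acceptance rates for testing and treatment are exposed in the same way, because people who agree to a study may also be readier to agree to a test or to treatment. With no control group, the primary percentage set against the 90% aim carries the effectiveness conclusion. What it means therefore depends on who is in the denominator.

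**Working it through.** The article gives no sample size or expected percentage to reproduce. The check is algebra on the denominator.

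**Inputs from the document (Background).** Linkage under full decentralization is 72%. Loss during treatment is 2.5% and after treatment 7.1%. In the earlier studies 0.50 × 0.53 = 26.5% of those testing positive started treatment.

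**Assumptions, not in the document.** Cure if linked, c = 90–95%. Consent if linked, a = 80–90%. Consent if not linked, b = 20–50%. Unlinked patients are not cured. Within the linked group, consent is unrelated to cure.

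**Step 1: reported against true percentage.** With linkage L:

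- true = L × c
- reported = L·c·a / (L·a + (1 − L)·b)

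True value: 0.72 × 0.90 = 64.8% to 0.72 × 0.95 = 68.4%.

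Reported value at the two extremes of the ranges:

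- a = 0.80, b = 0.50, c = 0.90: 0.5184 / (0.576 + 0.140) = 0.5184 / 0.716 = 72.4%
- a = 0.90, b = 0.20, c = 0.95: 0.6156 / (0.648 + 0.056) = 0.6156 / 0.704 = 87.4%

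With b = 0 the formula reduces to c, so 90–95% would be reported.

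**Step 2: cross-check with the document's losses on treatment.** Assume 100% SVR in those retained. True elimination is 0.72 × 0.975 × 0.929 = 65.2%. If a share q of the unlinked 28% is missing from the denominator, the reported value is 0.652 / (1 − 0.28q):

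| q | reported |
|---|---|
| 0 | 65.2% |
| 0.25 | 70.1% |
| 0.5 | 75.8% |
| 1 | 90.6% |

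With 95% SVR in those retained, the true value is 62.0% and the value at q = 1 is 86.0%.

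**Step 3: what a reported 90% would mean.** If a share f of RNA-positive patients never consents and is cured at rate c0, the percentage among all of them is (1 − f) × 90% + f × c0:

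| f | c0 = 0 | c0 = 50% | c0 = 90% |
|---|---|---|---|
| 5% | 85.5% | 88.0% | 90.0% |
| 10% | 81.0% | 86.0% | 90.0% |
| 20% | 72.0% | 82.0% | 90.0% |

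If the missing patients are all uncured, a true 80% reads as 90% once 1 − 0.80/0.90 = 11.1% are missing. A true 85% needs 1 − 0.85/0.90 = 5.6%. The last column shows no bias when non-consenters are cured as often as consenters.

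**The case against.** The strongest reply is that the article leaves consent timing open but nowhere says consent is taken late. Consecutive invitation of at-risk visitors points to enrolment by risk status, not by result. The study is prospective, and outcomes such as the number tested and the prevalence among those tested need people enrolled whatever their result. A patient not linked to HCV care may still attend a methadone post or outpatient clinic and can be asked there. Table 1 lists loss to follow-up as an endpoint, so losses among enrolled patients will be seen. Decliners treated on site and cured are missing too, which partly offsets the bias. Finally, a condensed article may leave consent logistics to the full protocol.

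Much of this stands. A reader might infer that the percentage is bound to be inflated, or that the study would declare 90% reached when the truth is near two thirds. The document does not support either. No combination within the assumed consent ranges reaches 90%; that needs b = 0, which lies outside them. The consent rates have no source in the article, and the 72% comes from a meta-analysis, not from these centres.

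What the reply does not remove is the mismatch. Invitation is not consent, and its timing relative to testing is not given. Even if the full protocol places consent before the test, decliners would still be absent from a denominator worded to include them.

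**Conclusion.** The point holds as a structural risk whose likely direction is upward. It is not a demonstrated bias. The article fixes a denominator of all identified RNA-positive patients, and its consent-based data capture cannot fill that denominator.

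The size cannot be derived from the document; the 72–87% reported for a true 65–68% is an illustration that depends on the assumed consent and cure rates. The worst case of 90–95% requires that no unlinked patient ever consents. The bias could also be small or absent: it is zero with full consent or with equal cure among non-consenters.

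The matter deserves a change to the plan because a modest uncounted share shifts how the result sits against the 90% aim, and because that share is hard to reconstruct later if centres did not count from the start.

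**What to change.** 1. Have each centre keep a short anonymous aggregate count of patients tested, RNA-positive, treated and with SVR, whether or not they consented. Use all RNA-positive patients in this count as the primary denominator.
2. If outcomes of non-consenters cannot be used, report how many RNA-positive patients did not consent and give two bounds, counting them all as not cured and all as cured. For example, a reported 90% with 10% not consented gives 0.90 × 0.90 = 81.0% and 0.90 × 0.90 + 0.10 = 91.0%.
3. State in Study population and Ethics that invitation and consent are sought at or before testing where feasible, and that testing does not depend on consent.
4. Name selection by consent among the limitations, and interpret the acceptance rates in that light.

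The cost is some clerical work at centres that receive no payment for taking part, and possibly a lower headline percentage. Seeking consent near the test also needs care, so that it does not deter people from testing in a low-threshold pathway.

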## Discussion

HCV viral elimination in line with WHO goals is within reach [4]. Micro-elimination efforts in target populations like PWUD are essential in countries with a low HCV prevalence in the general population like the Netherlands. This study aims to test a decentralization model tailored to population and system needs, aimed to integrate HCV care within addiction care, with the specific objectives to (1) test effectiveness in achieving 90% elimination viral elimination rates; and (2) explore facilitators and barriers for implementation of decentralized HCV care within addiction care.

Efficient, low-threshold treatment for HCV-infected PWUD is one strategy of HCV-micro-elimination to reduce the human reservoir of HCV and contribute to HCV elimination goals of the WHO [25]. The findings of this study will strengthen the evidence base for decentralized HCV-care within addiction care. Furthermore, identification of facilitators and barriers for implementation of a decentralized HCV-care model within addiction care can identify best practices and feed into a blueprint to support scaling-up of HCV care decentralization. Thus, the current study will contribute to achieving WHO HCV elimination goals.

We make use of the RE-AIM framework to systematically evaluate all necessary dimensions for successful implementation of decentralized HCV care. It has to be acknowledged that commonly not all dimensions of the RE-AIM framework are covered within a single study. This also applies to the current study, where research objective one provides information on both reach and effectiveness of the intervention in real life, and the qualitative research objective two will mainly provide information on implementation (see Table 1). If successful, future studies should explore maintenance of decentralized HCV care within addiction care.

**Table 1 Tab1:** Methods and endpoints in the RE-AIM framework

Quantative study endpoints: HCV care pathway (part 1)	RE-AIM dimension^a^	Qualitative study endpoints: barriers and facilitators (part 2)
• Demographics of population • Proportion of population tested	*Reach*	• Individual reasons for not participating • Recruitment of patients • Willingness to participate
• Viral elimination rate	*Effectiveness*	**–**
• Proportion of centers participating	*Adoption*	• Willingness to initiate the program
• Secondary HCV care endpoints (treatment uptake, completion) • Referral to hospital • Loss to follow up • Adherence	*Implementation*	• Strategies to improve implementation

^a^Maintenance is beyond the scope of this study but will be the focus of future studies

This study has multiple strengths. First, its nationwide implementation in different addiction care settings will ensure a heterogenic PWUD study population, increasing generalizability of findings. This allows us to translate our results to other addiction care facilities both in the Netherlands and other countries. Second, the mixed method design of this study allows for observational outcomes to be substantiated by qualitative findings that provide more in-depth information and understanding of the quantitative observations. Lastly, CAC efforts are guided by an experienced interdisciplinary team of behavioral scientists, addiction care experts, and viral hepatitis experts through HepNed. This will grant a unique opportunity to bridge the gap between addiction care and hospital care.

A limitation of this study is the lack of a control group, as the CAC pathway utilizes standard of care treatment. Also, we believe it would be unethical to deny patients in a control group safe and effective decentralized treatment, given the current evidence for decentralization of HCV care. Another limitation is that the ‘maintenance’ dimension of the RE-AIM model is beyond the scope of the study. The timeframe for this study does not include long-term follow-up. However, we do aim to establish low threshold communication between local hospitals and participating addiction care centers to fully integrate decentralized HCV care in the long-term. We therefore suggest to evaluate the long-term effect and adherence to implemented decentralized care models in future studies. Finally, it is important to note that not all PWUD seek care. In a field work study conducted in 2013, of 401 problematic opioid users (regular use with either criminal activity, comorbid psychiatry, or unstable lifestyle) 79.2% reported to have received addiction care in 2012. Based on this finding they estimated the size of the problematic opioid user population in the Netherlands at 14,000, a decline of 21% compared to 2009 [26]. Trends of problematic opioid use in addiction care in the Netherlands has since declined further, also their average age continues to rise, which indicates a minimal influx of new patients [27]. This means that there is a treatment gap, potentially hindering the reach of our intervention. However, given these findings our intervention within addiction care would still reach the majority of our target population.

To summarize, we will describe the nationwide implementation of CAC, a decentralized HCV care model for PWUD in the Netherlands. The study is aligned along the RE-AIM framework, aiming to contribute to HCV elimination among PWUD. Using a mixed methods approach, this study will substantiate current evidence for fully decentralized HCV-care, integrated in addiction care, and provide insights in potential facilitators and barriers for implementation and scaling-up of this decentralized HCV-treatment approach. This will contribute to achieving WHO hepatitis C elimination goals worldwide.

## Data Availability

Not applicable.

## Abbreviations

ACP: Addiction care physician
HBV: Hepatitis B virus
HCV: Hepatitis C virus
HIV: Human immunodeficiency virus
CAC: Hepatitis
C: Chain of addiction care project
DAA: Direct acting antiviral
IDU: Injection drug use
METC: Medical research ethics committee (MREC); in Dutch: medisch-ethische toetsings commissie (METC)
NISPA: Nijmegen institute of science-practitioners in addiction
OST: Opioid substitution therapy
PWUD: People who use(d) drugs
SD: Standard deviation
SVR: Sustained virological response
WHO: World Health Organization
